### Organization intervention/Operators

The operators of this study will be 10 dentists who work in the dental offices located at the public schools of Barueri. All operators will receive only a guideline of how to prepare, restore and finalize the restoration according to the original procedures of ART [2]. Regarding the procedures in the CT group, all the dentists will receive explanations about the preparation of the cavity according to partial caries removal philosophy and also about the manufactures’ specifications of the materials used. Since it is a pragmatic clinical trial, operators with different clinical expertise will be selected and no training will be performed for both groups.

### Intervention flexibility – delivery/Adherence

The intervention will be delivered and the flexibility of the trial will be similar to the usual care. The treatments will be done by the dentists of the municipality during their normal working setting.

The patient will be invited to participate of the research since they have matched the inclusion criteria. No extra encouragement to adhere to the study will be done.

### Participant selection

The criteria for caries presence will be the World Health Organization [11] and the DMFT and dmft will be recorded [12]. The biofilm evaluation according to the criteria proposed by Löe (1972) [13] and the gingival health [14] will be held before the restoration (baseline).

### Randomization

The randomization lists were computer generated (www.randomization.com), based on randomly permuted blocks of varying size (2, 4 or 6, randomly sampled with equal probability) and stratified for operator (1–10), dentition (primary/permanent) and surface (single/multiple). Opaque, sealed and sequentially numbered envelopes will be used to randomize the participants into the treatment groups (ART and CT).

### Study groups

Participants will be randomly assigned into two different groups:Atraumatic Restorative Treatment (ART) (control): ART-restorations using high viscosity glass ionomer cement (GIC) Ketac Molar EasyMix (3 M/ESPE) with manual dosage and hand-mix powder-liquid.Conventional Treatment (CT) (experimental): composite resin restoration, Scotchbond™ Universal Adhesive (3 M/ESPE) and the Filtek Bulk Fill composite resin (3 M/ESPE).

### Interventions

Atraumatic Restorative Treatment (ART) using Glass Ionomer Cement (GIC)The treatments from ART group will be performed according to the ART guidelines as described by Frencken et al. [15]. The isolation of the operating site will be done with cotton wool. The cavity will be opened with a dental hatchet and enamel cutters. Regarding the dentin caries removal, only will be removed the soft and completely demineralized dentine with hand excavators.For the dentin conditioning, will be used the first drop of 11.5 % polyacrilic acid with a microbrush during 15 s. Then, the cavity will be washed with three cottons moistened with water and dry using other three cotton pellets.After this step, the dosage (1:1 powder-liquid ratio) and hand mixing of the material will be made. The material only can be applied while it remains glossy. The GIC application will be done with a#1 spatula followed by finger pressure using petroleum jelly. In occlusal-proximal cavities, an adapted matrix with a wooden wedge must be used to provide an appropriate contour to the restoration.After the initial setting, the occlusion will be checked with articulating paper. A new layer of petroleum jelly should be applied on the surface of the restoration after removing the excess. The dentists will give instruction to the patient to not eat solid food for one hour.Conventional Treatment (CT) using Bulk Fill composite resinThe teeth in this group will be treated in a conventional way, which dentists are used to carry out followed by restoration with composite resin. As a routine program in public health center of Barueri, no rubber dam will be used.Instructions about the removal of carious tissue will be given, using a spherical carbide drill at low speed under refrigeration or using hand instruments, according to the operator preference.After the preparation of the cavity, no cavity conditioner will be applied, since the adhesive system used (Scotchbond™ Universal Adhesive - 3 M ESPE) allows the self-etch technique.The restoration will be performed using composite resin (Filtek Bulk Fill – 3 M ESPE). If the cavity size is bigger than 4 mm, two increments must be applied.For light curing, both for the adhesive system and the composite resin, the same light equipment will be used. If necessary, finishing bur will be used for adjustments.

### Follow-up

All the evaluations will be carried out by one single trained and calibrated evaluator (Kappa >0.70). The children that participated in the study will be localized by the national education system, regarding the school that they study, classroom and phone number.

An independent and calibrated evaluator will go to the school that the child studies after 6, 12 and 24 months to perform the evaluations.

The evaluation of the restorations will be held according to Roeleveld et al. [16] (Additional file 2). The width and depth of marginal defects, the surface wear and the excess or lack of material will be measured using the CPI periodontal probe which has a ball-shaped end-point of 0.5 mm in diameter.

### Outcomes

As a pragmatic trial, the outcomes must be relevant to the patient. So, the primary outcome of this study is the longevity of single and multiple-surfaces ART-restorations compared to Conventional Treatment (CT) in primary and permanent molars.

As secondary outcomes we will evaluate the technical preference assessment by dentists using an adapted and translated questionnaire [3] (Additional file 3) and the evaluation of the cost-effectiveness of the two techniques applied. The longevity of the tooth, in case of primary teeth will also be evaluated.(I)Longevity of the restorationTreatment longevity will be evaluated after 6, 12, 18 and 24 months by one trained and calibrated examiner. The intra-examiner and inter-examiner agreement will be calculated using the Cohen’s Kappa test and only scores above 0.7 will be accepted.Following on the Roeleveld et al. [16] criteria, it will be considered “success” only the restorations that receive the scores 00 and 10. The scores 11–40 will be considered “failure”. The scores 50, 60, 70 and 90 will not be assessed in the analysis of the success of the restoration.(II)Longevity of the toothThis outcome will be calculated only for the primary teeth included in this research. Intact restorations and the ones with a minor failure of the restoration (scores 00 to 30) will be considered as “success”, using the same criteria mentioned above [16]. Only the restored teeth that presents symptoms of pulp inflammation or need extraction (scores 40 and 50) will be considered as “failure”, since it cannot be considered as a successful treatment for the tooth.The main objective of a restoration is to provide a better condition for the patient by improving oral hygiene, inactivating the caries process, and returning the masticatory function of that tooth, so the scores considered “minor failures” will not be considered failure for the tooth [17].(III)Cost-effectivenessTo calculate the direct and indirect costs of the procedures, it will be taken into account the time spent on each treatment, including the treatment and the follow-up visits. The reference group to do the cost analysis will be the ART. The time spent in each session will be timed by a dental assistant (which is not participating in diagnostic tests or treatment) in order to input the cost-effectiveness analysis of the methods used in the research. All the information will be registered in predetermined sheets the specifications and quantity of all materials used.For the calculation of direct costs, it will also be considered the prices of materials used in each procedure based on an actual dental market value converted in US Dollars and obtained by the mean values from different dental stores for the referred products. In order to calculate the Professional Cost, we will calculate the time spent in each session and convert it in hours and multiply it by the medium income of the dentist per hour as related by the Brazilian Ministry of Labor and Employment ($36.23).To estimate the procedure cost, it will be considered both variable cost, which includes electricity and equipment depreciation, and material costs [18, 19]. To calculate the equipment depreciation (peripherals, dental chair and instrumental), we will consider their costs, the life span of five years and a monthly use of 160 h, using an estimate value per hour of $1.81.(IV)Preference of the treatments by dentistsThe preference of dentists will be evaluated at the end of the operative phase. Thus, we aim to identify which is the preferred procedure by professionals. To evaluate this outcome, a questionnaire composed of six items will be applied.This questionnaire was adapted from the study of Pani et al. [3], which evaluated the preference of students with respect to composite and silver amalgam. The questionnaire was translated from English to Portuguese by a Brazilian dentist who is fluent in both languages and was adapted for comparing the composite resin and the glass ionomer cement used according to the ART. This questionnaire will be administered before and after the research for the dentists (Additional file 3).

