**Methods/design:**

A total of 1,214 5-to-13 year-old children with at least one single or multiple-surface dentin caries lesion in primary or permanent molars will be selected in public schools of Barueri-SP, Brazil. The participants will be randomly assigned into 2 groups: CT (caries removal with bur and restoration performed with Scotchbond™ Universal Adhesive system associated with Filtek Bulk Fill – 3 M/ESPE) and ART (Caries removal with hand instruments and restoration with high viscosity glass ionomer cement Ketac Molar Easy Mix – 3 M/ESPE). Ten untrained dentists will perform the treatment in in dental offices located at public schools. The restorations will be evaluated after 6, 12 and 24 months by an independent trained and calibrated examiner. The restoration and tooth survival, the cost-effectiveness analysis between the two groups and the operators’ preferences regarding the techniques will be also evaluated. Kaplan-Meier survival analysis and log-rank test will be applied for the restoration and tooth survival. All the average event rates in the two groups will be modelled and compared with a Cox proportional hazard shared frailty model since there is an operator-cluster effect. The significance level for all analyses will be 5 %.

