### Ethical aspects and registration

This clinical trial was approved by the Local Ethics Committee of Research in Humans (#1.293.897) and registered in the database for registration of clinical studies Clinicaltrials.gov (registration no. NCT02568917).

The study will be conducted in Barueri, a city in the state of São Paulo, Brazil. Informed consent will be obtained from children’s parents or guardians before participation in the study and each child must also assent to participate.

All participants will be encoded by a number in order to guarantee information confidentiality. In case of files containing identifiable data, those will be stored in locked filing cabinets and final dataset will be available for inspection under coordinator’s endorsement. Thus, there is no Data Monitoring Committee. Only researchers will have access to participants’ information. Independent surveillance of trial data collection, management and analysis is undertaken by the main investigator ([name]) who has overall responsibility for the study and is in charge of the data. The collected data will be subject to audition by the coordinator; by raising data queries if necessary. This protocol has been peer-reviewed by the funding agency.

The adverse events related to the CT or ART (groups investigated in this trial) are those related to dental treatment. These effects are similar to those found during a conventional treatment performed in the pediatric dentistry clinical practice. The operators of this project will conduct all dental treatment needs of the children participating in this trial.

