### PRECIS (Pragmatic-Explanatory Continuum Indicator Summary) domains

#### Elegibility/Recruitment/Setting

The participants of the trial are those who would receive dental treatment in a usual care. No extra effort will be made to recruit more participants. All children that have at least one single or multiple-surface caries lesion in a primary or permanent posterior tooth and who seek for treatment in one of the participating centers are eligible for this trial.

Only the children whose parents or legal guardians signed the informed consent and who assent to be part of the study will be included in the research. All phases of this trial will be carried out in the dental clinic located at public schools. As radiographic facilities are not available in this setting, only clinical diagnosis will be used.

As this trial aims to evaluate the restoration and tooth survival, the tooth of interest should not present any associated fistula, abscess, pulp exposure, historical of spontaneous dental pain or mobility.

Even when children do not present a cooperative behavior, they will be included in this trial, as it is a common problem in pediatric dentistry clinical practice. Other variables like size of the cavity, approximal or occlusal contact and caries experience will also not be considered as exclusion criteria. All data will be recorded and further analysed to manage if there is any influence of those clinical factors on the survival rate of the restorations.

Recruitment will take place from March to November 2016. Each participant will be enrolled in the study for about 25 months: 1 month for RCT diagnosis and treatment, followed by a 24-month observational period. Details are illustrated in Fig. 1.

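### The examination schedule for the primary outcome contradicts itself (with or without an 18-month visit), and the printed scoring rule can miss or exclude failures treated between visits

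*Protocol article*

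**What the plan says.** Three places in the protocol article state when restorations are examined.

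- Outcomes, (I) Longevity of the restoration: "longevity will be evaluated after 6, 12, 18 and 24 months by one trained and calibrated examiner".
- Follow-up: the evaluator "will go to the school that the child studies after 6, 12 and 24 months to perform the evaluations".
- Abstract, Methods/design: "The restorations will be evaluated after 6, 12 and 24 months by an independent trained and calibrated examiner".

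The Eligibility/Recruitment/Setting section adds a total duration, "1 month for RCT diagnosis and treatment, followed by a 24-month observational period", which fits either schedule.

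The Outcomes section classifies a restoration by its score at examination: "it will be considered “success” only the restorations that receive the scores 00 and 10". Scores 11 to 40 are failures. Then: "The scores 50, 60, 70 and 90 will not be assessed in the analysis of the success of the restoration". For the secondary outcome of tooth longevity (primary teeth only), the same section counts scores 40 and 50 as failures and describes them as pulp inflammation or need for extraction. The article does not define codes 60, 70 and 90; it refers to Additional file 2 for the criteria.

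The Ethical aspects section says: "The operators of this project will conduct all dental treatment needs of the children participating in this trial". The Data analysis section applies Kaplan-Meier, log-rank and a Cox shared-frailty model, with each participant included up to the last available time point.

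**The concern.** The three statements on timing cannot all be followed. They concern the primary outcome, and an examination-based endpoint takes its event dates from the visits. Whether there is an 18-month visit decides whether the last unobserved interval is 6 or 12 months, where failures in the second year are placed on the curve, and how much follow-up a child lost late contributes. The cost analysis counts time spent in follow-up visits, so it may be affected too.

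The second part concerns what happens between visits. The operators look after all treatment needs, so some study teeth can be expected to be redone or extracted before the evaluator next sees them. A rule based only on the examination score does not say how such a tooth is counted. One score that marks a tooth failure is also removed from the restoration analysis. Failures could therefore drop out of the primary endpoint. Operators are unblinded, and their technique preference is named in the Data analysis section as a contextual variable, so the loss need not be equal in the two arms.

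**Working it through.** **1. The plan's own sample size.** Inputs from Sample description and Table 1: two-sided 5%, power 80%, ART survival at 2 years of 93, 62 and 41%, differences of 15 or 20 points. Freedman's log-rank formula with HR = ln(S2)/ln(S1) and N = events / mean event probability gives:

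| Comparison | HR | Events | Mean event probability | N | Stated |
|---|---|---|---|---|---|
| 93 vs 78% | 3.424 | 27 | 0.145 | 186 | 181 |
| 62 vs 82% | 0.415 | 46 | 0.28 | 164 | 165 |
| 41 vs 61% | 0.554 | 96 | 0.49 | 196 | 195 |

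Multiplying the stated N by 1.4 and 1.2 leads to 304 + 278 + 304 + 328 = 1,214. The plan's figures are reproduced closely. None depends on the number of visits, so 1,214 stands.

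**2. Failures whose date depends on the schedule.** Assume a constant hazard, so S(t) = S24^(t/24). The share of 24-month failures falling in months 12-18 is (S12 - S18)/(1 - S24).

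| S24 (ART) | S12 | S18 | S12 - S18 | 1 - S24 | Share |
|---|---|---|---|---|---|
| 0.93 | 0.964 | 0.947 | 0.017 | 0.07 | 25% |
| 0.62 | 0.787 | 0.699 | 0.089 | 0.38 | 23% |
| 0.41 | 0.640 | 0.512 | 0.128 | 0.59 | 22% |

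The comparison rates used in step 1 (78, 82, 61%) give 24, 24 and 23%. These failures are dated 18 months under one schedule and 24 under the other.

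**3. The curve at month 18.** Without an 18-month visit the Kaplan-Meier curve keeps its 12-month value until month 24. At month 18 it reads 64% instead of 51% (41% stratum), 79% instead of 70% (62%), and 96% instead of 95% (93%). With complete follow-up, the 24-month estimate is the same under both.

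**4. Censoring.** A child lost between months 18 and 24 contributes 18 months under one schedule and 12 under the other. Under the shorter list, that child's failure in months 12-18 is never seen. The plan allows 20% for losses.

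**5. Power.** Simulation: exponential failure times, failure recorded at the next visit, log-rank test, 4,000 runs, the same failure times under both schedules, stated base N, no dropout or clustering.

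| Comparison | Visits 6/12/24 | Visits 6/12/18/24 |
|---|---|---|
| 93 vs 78%, N = 181 | 83.3% | 83.2% |
| 62 vs 82%, N = 165 | 83.0% | 83.0% |
| 41 vs 61%, N = 195 | 80.1% | 80.4% |

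**6. Ties.** In 20 simulated datasets of 6,000 teeth (41 vs 61%, true HR 0.554), Breslow ties gave about 0.60 with three visits and 0.58-0.59 with four. Efron ties gave 0.55-0.56 under both.

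**7. Teeth treated between visits.** Under the printed rule, a tooth redone or extracted before the next visit can take one of three routes:

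- a score of 00 or 10, counted as success;
- a score from 11 to 40, counted as failure;
- a score of 50, 60, 70 or 90, not assessed.

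Only the second keeps the failure in the primary analysis. Score 50 shows that the third route can remove a real failure, since the same section counts it against the tooth.

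**The case against.** The strongest reply on timing is that the conflict is a slip with little numerical consequence. A failure in months 12-24 is counted by month 24 either way, and neither power nor sample size moves. That stands for the overall comparison when both arms have the same visits and follow-up is complete. It does not settle curve shape, intermediate estimates or late losses. The assessment diagram (Fig. 1) is not shown, but it could not make the conflicting statements agree.

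On interim treatment, a reader might infer that repaired failures will be scored 00 or 10 and so become successes. The article does not support that. The code definitions are in Additional file 2, which is not shown, and a redone restoration might have its own code. What the article does show is a rule based on examination scores alone and the exclusion of score 50.

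A reader might also put a size on this. If 10-30% of failures were repaired unseen and scored as success, 24-month survival would be overstated by that share times (1 - S24): 0.7-2.1 points at 93%, 3.8-11.4 at 62%, 5.9-17.7 at 41%. The share is purely an assumption, and the result is an error in one arm's absolute survival, not in the difference between arms. It should not be cited as an estimate.

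The tie point is fairly called analysis-plan detail: the article names no tie method, and an ordinary Efron option already removes nearly all the bias.

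Finally, counting operators' repairs as failures gives unblinded operators some influence over the endpoint. That objection is sound and shapes the fix.

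**Conclusion.** The schedule contradiction is established by the text and should be reconciled. Its size is moderate for event dating and small for inference. Under a constant hazard, at the plan's ART rates and the comparison rates that reproduce its sample sizes, about 22-25% of 24-month failures change date. The 18-month reading shifts by up to 13 points (64 - 51). Simulated power changes by less than 0.5 points in those settings, without dropout.

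The gap in the scoring rule is established only as a possibility: true failures may be missed or excluded, pending Additional file 2. Neither its extent nor any difference between arms can be derived from the article.

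**What to change.** 1. Reconcile the Abstract, Follow-up and Outcomes sections to one examination schedule, identical in both arms. Cost: a wording change.
2. Check Additional file 2 for how redone restorations and lost teeth are coded. Then state in the outcome rule that a study restoration recorded as repaired or replaced because it failed, or a tooth lost to pulp disease or extraction (not natural exfoliation), is a failure in the visit interval in which it was recorded. Reconcile this with the exclusion of score 50.
3. Add a sensitivity analysis using the examiner's scores only, because the operators are unblinded.
4. As secondary advice, specify Efron or exact ties, or a grouped-time model, since failures fall on three or four dates. Cost: a standard model option.

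The main costs are that a flag must be taken from operators' records, whose content the article does not describe beyond time and materials, and that part of the endpoint then rests on unblinded operators. The sample size does not change.

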
### Data analysis

Data will be analyzed according to the protocol principle. First, to compare treatments’ and teeth longevity, both Kaplan-Meier survival analysis and Log-rank test will be applied. The association between restoration longevity and caries experience or type of cavity will be evaluated using Cox Regression.

As we have a cluster-effect related to the numbers of operators of this trial and its contextual variables (such as age, work experience and technique preference), the average event rates in the two groups over the two year study period will be then modelled and compared with a “shared frailty” model. This model is an extension of the Cox proportional hazard model that includes a frailty term (a statistical expression for random effect, unrelated to the clinical concept of frailty) to take dependency of events within a contextual (correlation between different falls by the same operator) into account. All participants will be included in the model until their last time point, which means that the model will use all available data right up to the time of withdrawal or trial completion. For each outcome, we will present the hazard ratios and 95 % confidence intervals for the intervention, adjusted by operator.

The variance analysis will be used to compare groups in relation to the cost after determining data normality through the Kolmogorov-Smirnov test. Poisson analysis will be used to assess the association between the treatment group, the preference of professionals and the cost of treatments. The significance level will be set in 5 %.

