In order to evaluate the preferences of dentists and measure a professional-centered outcome, a questionnaire composed of sixteen items will be applied [3]. It aims to evaluate factors influencing dentists’ preference of amalgam or composite for posterior dental restorations, which can influence the quality of the restorations.

The growing use of cost-effectiveness analysis (CEA) to evaluate the costs and health effects of specific interventions is dominated by studies of prospective new interventions compared to current practice [21]. The dental treatments (ART and CT) are daily performed during the normal clinical practice, but maybe with different materials (there is a large range of materials available in Brazilian market). In order to standardize the materials that will be used in this trial, we received a donation from the manufacturer. There is no conflict of interests, and the results will be published in good quality journals.

The patients of this trial will be children who study in the school where the dental office is located. Even it is not the best pragmatic way to perform the follow-up, the evaluation will be done by a single evaluator, in a school setting, in order to reduce drop-outs during the follow-up. This evaluation system is possible since we can locate the child aided by a national student’s data website [22].

Regarding our main outcome, to evaluate the survival rate of the ART and CT restorations, we chose the Roeleveld criteria [16], that allows splitting the evaluations in minor and major failure [23], therefore the survival of the tooth (in case of primary dentition) can also be calculated. The objective of a restoration is to provide the patient a condition for arresting caries lesion and avoid pulp problems or extractions. For that reason, studies should focus on the survival of the restored teeth and not remain limited to the minor failures of restoration survival [24, 25].

The ART is already well described in the literature, both in primary and permanent teeth [10, 26, 27] and well accepted by dentist due to its ease of use. In another hand, little is known about bulkfill composite resin, which can also be used as an aesthetic restoration and in one single increment. In that way, this pragmatic study will contribute to improve the knowledge about the ART and CT for restoring single or multiple surface carious lesions in primary and permanent dentition.

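### Costed follow-up time appears to be the evaluator's research examinations, so cost totals depend on length of follow-up while the cost comparison does not allow for it

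*Protocol article*

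**What the plan says.** Outcomes, item (III) Cost-effectiveness, defines the time component of cost: "it will be taken into account the time spent on each treatment, including the treatment and the follow-up visits". "The time spent in each session will be timed by a dental assistant", and that time is converted to hours and multiplied by a dentist's hourly income of $36.23. Equipment depreciation is added, "using an estimate value per hour of $1.81".

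The follow-up visits that the protocol describes are outcome assessments. Under Follow-up: "An independent and calibrated evaluator will go to the school that the child studies after 6, 12 and 24 months to perform the evaluations". Outcomes item (I) lists four assessments, at 6, 12, 18 and 24 months. The Discussion comments on this arrangement: "Even it is not the best pragmatic way to perform the follow-up, the evaluation will be done by a single evaluator, in a school setting". It gives the reduction of drop-outs as the reason.

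Under Data analysis, "The variance analysis will be used to compare groups in relation to the cost", after a Kolmogorov-Smirnov check of normality. The rule that participants contribute data until they leave is written for the shared frailty model. Nothing similar is written for cost, and the section does not say which teeth enter the cost comparison.

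**The concern.** Two stated choices combine badly. The first puts follow-up visit time into each tooth's cost. If those visits are the evaluator's examinations, the trial charges both treatments for an activity that exists only because of the trial. The second compares the resulting totals by a method that treats every total as complete. A child who leaves after the 6-month examination has one priced visit. A child who stays has three, or four under the Outcomes schedule. Part of the recorded cost then measures how long the child was followed, not what the care cost.

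Superior cost-effectiveness of ART is the hypothesis stated in the Abstract, and cost-effectiveness is a named secondary outcome. A cost difference that moves with withdrawal would be hard to defend to the policy makers for whom the result is meant. The point is separate from whether re-treatment is costed. It would arise even if every re-treatment were captured.

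**Working it through.** The protocol gives no cost total, visit length or loss by arm, so there is no cost figure of its own to reproduce.

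**Inputs from the document.** Professional time $36.23 per hour and equipment $1.81 per hour (Outcomes, item III); three visits (Follow-up) or four (Outcomes, item I); planned losses of 20 % overall, not split by arm (Sample description).

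**Assumptions.** 2, 5 or 10 minutes per visit; withdrawn teeth stay in the comparison; losses of 15 % and 25 %, chosen to average the planned 20 %.

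**Step 1, price of a visit.** Hourly rate = 36.23 + 1.81 = $38.04. Cost per visit = 38.04 × minutes / 60.

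**Step 2, visits attended with three planned.** With loss proportion L, the mean is 3 − 3L if all losses fall before 6 months. If losses are spread evenly over the three intervals, it is (1 − L/3) + (1 − 2L/3) + (1 − L) = 3 − 2L. For 15 % against 25 %, the arms differ by 3 × 0.10 = 0.30 visits (all early) or 2 × 0.10 = 0.20 visits (even).

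**Step 3, shift in the mean cost difference** = visits difference × cost per visit.

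| Minutes per visit | Per visit | Three visits | Four visits | Shift, even losses | Shift, all early |
|---|---|---|---|---|---|
| 2 | $1.27 | $3.80 | $5.07 | $0.25 | $0.38 |
| 5 | $3.17 | $9.51 | $12.68 | $0.63 | $0.95 |
| 10 | $6.34 | $19.02 | $25.36 | $1.27 | $1.90 |

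The two shift columns are for three visits. Losses of 10 % against 30 % double them ($0.51 to $3.80 overall). Losses of 20 % in both arms with the same timing give $0. Equal losses with different timing do not cancel: 20 % all early gives 3 − 0.60 = 2.40 visits and 20 % spread evenly gives 3 − 0.40 = 2.60, again a gap of 0.20 visits.

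**Scale.** An assumed 25-minute treatment session costs 38.04 × 25 / 60 = $15.85 before materials. The range $0.25 to $1.90 is about 2 % to 12 % of that.

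**Effect on the test.** A simulation with equal true costs (2,000 runs; 5-minute visits; treatment time mean 25, SD 8 minutes; no materials; all assumed) gave these false-positive rates at the 5 % level. Each range runs from even to all-early losses.

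| Losses | 152 teeth per arm (304/2) | 607 per arm (1,214/2) |
|---|---|---|
| 20 % vs 20 % | about 4 to 5 % | about 4 to 5 % |
| 15 % vs 25 % | 16 to 25 % | 49 to 75 % |
| 10 % vs 30 % | 50 to 75 % | 97 to 100 % |

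**Relative comparison, with no difference in losses.** Assumed sessions of 30 and 24 minutes cost $19.02 and $15.22, a saving of 20 %. Adding three 5-minute visits to both gives $28.53 and $24.73, a saving of 13 %. Adding three 10-minute visits gives $38.04 and $34.24, a saving of 10 %. The absolute difference stays at $3.80 throughout.

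**The case against.** The protocol never says outright that the costed visits are the evaluator's. Timing by a dental assistant, a dentist's hourly income and depreciation of a dental chair fit clinical sessions at least as well as a school examination with a probe. Operator return visits are also foreseeable, because Ethical aspects has the operators meet all the children's dental treatment needs. The Discussion's remark on follow-up concerns who evaluates and where, not cost. This stands in part: the link is an inference. But no other follow-up visit is described, and the same words are used for the evaluator's schedule.

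The bias is also conditional. Children are located through school records in both arms alike, and a child with teeth in both arms leaves both at once. If the cost analysis is restricted to completers, no truncated total enters it. All of this stands. A reader might infer that the planned comparison is biased as it is written, or that it will favour one named treatment. The document supports neither: it gives no loss by arm, does not say that withdrawn teeth are kept, and gives no reason to expect more losses in one arm.

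A cost added equally to both arms cancels in the absolute difference, which is what analysis of variance tests. That stands too. Only a percentage comparison is diluted, and the protocol names none.

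Finally, handling of incomplete costs is commonly left to an analysis plan, and one may exist. Its absence from the article is therefore not the point. The cost definition and the method of comparison are both stated here, and it is their combination that needs attention.

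**Conclusion.** The point holds in conditional form. On the natural reading, time spent on research examinations is priced into the cost of each tooth, and a component that grows with length of follow-up is compared by a method that ignores it. If withdrawn teeth are kept and losses differ between arms in number or timing, the arm with more or earlier losses is recorded as cheaper than it really is. That arm need not rank as the cheaper one.

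Under the stated assumptions the shift runs from cents to a few dollars per tooth. It is zero when losses match in number and timing. Visit length, loss by arm and treatment time are all assumed, so neither the dollar figures nor the simulated error rates are predictions for this trial. With matched losses, what remains is added noise and dilution of any relative figure. This is an inexpensive improvement to a secondary outcome. The primary survival comparison is not affected.

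**What to change.** In Outcomes item (III), define cost as the time, materials and equipment of the restorative session or sessions, plus any operator visits for the study tooth. State that the evaluator's protocol examinations are not costed. This removes the dependence on withdrawal described here, and the mismatch between three and four assessments no longer alters the cost total. In Data analysis, state which teeth enter the cost comparison.

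Only if costs that accrue over follow-up are kept, such as operator return visits, compare the arms over a fixed 24-month horizon with a method that allows for censoring. Inverse-probability-weighted mean cost by follow-up interval is one example.

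The price is a change of wording, lower reported total costs and slightly more analysis work. The recording sheets are not shown, so check that they separate operator sessions from evaluator examinations.
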